## Abstract

**Background:**

Intensive motor learning interventions, such as Hand-Arm Bimanual Intensive Therapy Including Lower Extremities (HABIT-ILE), have demonstrated significant improvements in upper and lower extremity functions, as well as in bimanual performance and activities of daily living in children with cerebral palsy. However, the typical delivery of HABIT-ILE as a 2-week on-site camp can be inaccessible to families living in remote areas or with travel difficulties. Offering HABIT-ILE as a home-based telerehabilitation program could overcome these barriers.

**Objective:**

The study aims to evaluate the effectiveness of this approach through 2 randomized controlled trials.

**Methods:**

A total of 44 children with bilateral cerebral palsy (aged 5‐18 years) will participate. HABIT-ILE@home will follow the principles of HABIT-ILE on-site but will be delivered at home with the involvement of caregivers and remote supervision by trained therapists. A dedicated virtual device will facilitate intervention delivery and remote monitoring (REAtouch Lite). The first randomized controlled trial (RCT), RCT1, will assess the noninferiority of high-dose HABIT-ILE@home vs on-site HABIT-ILE (65 h over 2 weeks, 6.5 h/d). The second RCT (RCT2) will assess the superiority of a HABIT-ILE@home follow-up program delivered over 9 weeks compared to a nonspecific home follow-up (45 h in total, 5 h/wk). The Gross Motor Function Measure-66 (GMFM-66) is the primary outcome. Secondary outcomes include feasibility and adherence questionnaires, motor and functional outcome measures, as well as activities of daily living questionnaires, self-esteem, participation in life situations, and neuroimaging. Evaluations will be conducted before (T0) and after (T1) the 2 weeks of therapy, followed by a final assessment after the follow-up (T2).

**Results:**

Recruitment was completed in June 2024. All interventions were performed by November 2024. Data analysis was completed in May 2025.

**Conclusions:**

The results will first confirm or refute the noninferior efficacy of a telerehabilitation HABIT-ILE@home program compared to its typical on-site delivery. Second, the results will determine the added value of a specific HABIT-ILE@home follow-up after such high-dosage motor learning–based interventions.

## Introduction

### Background

Cerebral palsy (CP) represents the most prevalent cause of physical disability in the pediatric population, affecting 1 to nearly 4 children in 1000 newborns worldwide [1,2]. This major public health problem, caused by abnormalities in or damage to brain development, results in a range of symptoms that vary widely from child to child. While all children with CP will develop motor symptoms such as postural and movement control deficits, some will also develop additional nonmotor symptoms, including pain (75%), intellectual deficits (50%), language disorders (25%), epilepsy (25%), and behavioral and sleep disorders (20%‐25%) [3]. The consequences of these symptoms may vary in severity but are typically manifested as long-term functional limitations in daily activities, including dressing, eating, and personal hygiene [4].

To enhance individual motor function and functional performance, intensive therapies based on motor skill learning (MSL) have been demonstrated to be particularly efficacious [5]. Among these interventions, Hand-Arm Bimanual Intensive Therapy including Lower Extremities (HABIT-ILE) has been developed over the last decade with the purpose to simultaneously engage upper and lower extremities as well as trunk control through bimanual manipulative activities performed while sitting on a ball, standing, or walking [6]. HABIT-ILE has led to notable improvements in upper and lower extremity functions, as well as in bimanual performance and activities of daily living for children with bilateral and unilateral CP [6,7]. A previous study [8] has shown that upper extremity improvement was not attenuated by the simultaneous engagement of both the upper and lower extremities compared to a similar intervention solely focusing on the upper extremities. In addition, the HABIT-ILE approach has been demonstrated to facilitate significant enhancements in social participation and a reduction in mirror movements among children with unilateral CP [9]. The motor and functional improvements observed following HABIT-ILE seem to be linked to changes in cerebral activity, as evidenced by changes in the fronto-parietal and cerebellum networks, as well as in the integrity of corticospinal tract fibers [10,11]. The intervention is typically delivered as a 2-week rehabilitation camp, comprising 50 to 90 hours of on-site activities [12-14].

However, this mode of delivery raises limitations in terms of accessibility and scalability. The implementation of a 2-week day camp necessitates considerable commitment from families, who frequently must travel to reach the therapy site. As the number of locations offering HABIT-ILE therapy is currently limited, families who live a long way from the facility and who are unable to travel cannot benefit from this therapy. Moreover, the organization of such intensive therapies continues to represent a significant challenge, given the necessity for a relatively spacious training room, a substantial quantity of equipment, and the involvement of trained therapists [15]. To address these concerns, the introduction of a home-based HABIT-ILE telerehabilitation program combined with caregiver coaching may represent an alternative solution. Virtual devices may be an effective means of implementing MSL principles and facilitating remote communication with families [16]. The range of telerehabilitation devices is vast, from classic video games [17] to devices specifically designed for rehabilitation purposes [18-20]. Although not all devices appear equally effective in implementing all principles of MSL during virtual-based-interventions, these principles can be applied with specifically-designed devices and the supervision of a trained therapist [16].

Besides the accessibility and organizational limitations related to intensive interventions, no specific follow-up intervention has so far been provided to participants at the end of a HABIT-ILE camp to facilitate the transfer of skills at home [6-8]. Maintaining the skills acquired during the 2-week intervention requires daily practice to avoid an unfavorable motor cortical reorganization and a loss of the newly developed skill [21,22]. As such interventions are frequently conducted outside conventional health care settings that oversee children throughout the year, transmission of information might sometimes be challenging to ensure continuity of care for children [21]. Accordingly, it may be beneficial to investigate the efficacy of a specific low- to moderate-dosage HABIT-ILE home-based follow-up program delivered after a 2-week HABIT-ILE therapy to increase the possibility to transfer the newly learned abilities at home and promote further improvements.

### Aims and Hypotheses

Two randomized controlled trials (RCTs) are described in this protocol. The first RCT (RCT1) aims to evaluate whether a high-dosage HABIT-ILE telerehabilitation intervention (HABIT-ILE@home) can achieve improvements in motor and functional abilities, as well as in social participation and neuroplastic changes comparable to those obtained with a conventional high-dosage HABIT-ILE on-site camp in children with bilateral CP aged 5-18 years. Gross motor function, assessed using the Gross Motor Function Measure-66 (GMFM-66), will constitute the primary outcome measure. We hypothesize that significant improvements in gross motor function will be observed in both groups after the 2-week intervention and that improvements achieved following HABIT-ILE@home will be noninferior to those observed after the HABIT-ILE on-site camp.

The second RCT (RCT2) aims to determine whether a structured low- to moderate-dosage HABIT-ILE@home follow-up program provided over 9 weeks leads to greater retention and further improvement in motor and functional abilities as well as in social participation, compared to a nonspecific home follow-up intervention based on usual clinical practice following the intensive HABIT-ILE intervention. Gross motor function assessed using the GMFM-66 will constitute the primary outcome measure. We hypothesize that children receiving the specific HABIT-ILE@home follow-up intervention will demonstrate greater retention and additional improvements in gross motor function compared with children receiving the nonspecific home follow-up intervention.

## Methods

### Study Design

For RCT1, 44 participants will be randomized to 1 of the 2 groups (“HABIT-ILE@home” or “HABIT-ILE on-site camp,” 65 h for 2 wk), 22 children per group (Figure 1). The HABIT-ILE on-site camp will take place in Belgium with the presence of interventionists and a supervision team, whereas the HABIT-ILE@home intervention will take place at the children’s home with the constant presence of a caregiver (eg, parents, relatives, or other close individuals) and intermittent remote supervision. After this high-dosage camp, each group will then be further randomized into 2 subgroups of 11 participants (RCT2). One subgroup will receive the specific HABIT-ILE@home follow-up (5h/wk, for 9 wk), while the other will receive a nonspecific home follow-up based on their usual therapist’s recommendations. Recommendations of practice schedule given to caregivers will be similar for both follow-up groups: 5 hours per week at home for 9 weeks. Participants will be assessed before (T0) and after (T1) the 2 weeks of HABIT-ILE high-dosage camp, as well as at the end of the 9-week follow-up (T2). This study protocol is reported in accordance with the SPIRIT (Standard Protocol Items: Recommendations for Interventional Trials) guidelines (Figure 2).

**Figure 1. F1:**
[figure not shown]
Study design for the implementation of Hand-Arm Bimanual Intensive Therapy Including Lower Extremities (HABIT-ILE) interventions in children with bilateral cerebral palsy (BCP). Forty-four children with BCP will be randomly assigned to either the HABIT-ILE@home group (n=22) or the HABIT-ILE on-site group (n=22). Both groups will complete an intensive 65-hour intervention over 2 weeks (T0-T1). Subsequently, each group will be further divided for a 9-week follow-up phase (T1-T2): half will continue with HABIT-ILE@home follow-up (n=11 per initial group), while the other half will engage in nonspecific follow-up home-based activities (n=11 per initial group). The timeline indicates assessment points at T0 (baseline), T1 (post intensive phase), and T2 (end of follow-up phase). h: hour; RCT: randomized controlled trial.

**Figure 2. F2:**
[figure not shown]
Study flowchart and data collection. Eligible children will be randomized into 2 groups: HABIT-ILE@home or Hand-Arm Bimanual Intensive Therapy Including Lower Extremities (HABIT-ILE) on-site therapy, followed by a second randomization into HABIT-ILE@home follow-up or nonspecific home follow-up subgroups. Data collection will occur at 3 time points: baseline (T0), post therapy (T1 = T0 + 15 days), and post follow-up (T2 = T0 + 90 days). Outcome measures will assess body functions, activities, participation, and feasibility across the study phases. BoHA: Both Hands Assessment; COPM: Canadian Occupational Performance Measure; CP: cerebral palsy; DTI: diffusion tensor imaging; fMRI: functional magnetic resonance imaging; GMFM-66: Gross Motor Function Measure-66; GMFCS: Gross Motor Function Classification System; MACS: Manual Ability Classification System; MFPT: Manual Form Perception Test; PEDI-CAT: Pediatric Evaluation of Disability Inventory–Computer Adaptive Test.

### Recruitment

#### Participants

For this study, 44 children with bilateral CP aged 5-18 years will be included. Children will be recruited in Belgium and surrounding countries based on contacts with reference centers at Belgian hospitals or via spontaneous applications, notably following information on social networks.

#### Inclusion Criteria

Children will be considered eligible if they are aged 5-18 years, have a confirmed diagnosis of bilateral CP, and have sufficient cognitive skills to play simple games (ie, throwing a ball) and follow simple instructions. For the needs of the HABIT-ILE@home intervention program, a caregiver (ie, family member, relatives, and so on) must be available for 6.5 hours per day to accompany the child for the 2-week HABIT-ILE@home therapy and during 5 hours per week over the 9-week HABIT-ILE@home follow-up.

#### Exclusion Criteria

Children will not be eligible to participate if they present uncontrolled seizures, have had botulinum toxin injections, orthopedic surgery, or intensive therapy within the past 3 months, or if such interventions are planned during the study period, or if they present with severe visual or cognitive impairments interfering with treatment and/or assessments, or if they have any contraindications for magnetic resonance imaging (MRI).

### Randomization Process

At the end of the recruitment phase, children were paired by the investigators according to Manual Ability Classification System (MACS) level, Gross Motor Function Classification System (GMFCS) level, and age, in this order of priority. Within each pair, participants were randomly assigned a code number (1 or 2) using Research Randomizer. To ensure allocation concealment and limit selection bias, the correspondence between the code number and the intervention group was determined independently by a person from an affiliated laboratory who was not involved in recruitment, assessment, or intervention delivery. This person indicated whether code 1 corresponded to the control group or to the treatment group after the pairs and code numbers had been generated. For RCT2, participants within each group of RCT1 were randomized again according to the same procedure to either the HABIT-ILE@home follow-up or the nonspecific home follow-up group (Figure 1).

### Sample Size

#### RCT1: High-Dosage Intervention (2-Week Home vs On-Site Camp)

Sample size calculation was performed using PASS (version 14.0.15; NCSS) for a one-sided noninferiority *t* test comparing 2 independent means. The analysis was based on the mean improvement in GMFM-66 observed in the study of Bleyenheuft et al [7]. We hypothesized that there would be a true difference of Gross Motor Function Measure (GMFM) units between groups, with an α of .05 and a 1-*β* of 0.9. We estimate that the noninferiority margin (NIM) could reach a maximum of 2 GMFM units since this value is the minimal clinically important difference (MCID) of the GMFM-66. The data are drawn from populations with SDs of 1.9 GMFM units. Consequently, 17 participants are needed per group (N=34). Considering 25% potential dropouts per group, 44 participants will be included.

#### RCT2: Low- to Moderate-Dosage Home Follow-Up Interventions (9-Week HABIT-ILE@home Follow-Up vs Nonspecific Home Follow-Up)

For RCT2, sample size calculation was also performed using PASS (version 14.0.15; NCSS) for a 2-sided superiority *t* test comparing 2 independent means. The analysis was based on the mean improvement in GMFM-66 observed in the study of Bleyenheuft et al [7]. In that study of school-aged children, the duration of the intervention was 84.5 hours and the GMFM-66 increased by 7 GMFM units. We thus hypothesized that, for 45 hours of intervention, there would be a true difference of 3.75 GMFM units between groups, with an α of .05 and a 1-*β* of 0.8. We estimate that the superiority margin will be 2 GMFM units since this value is the MCID of the GMFM-66. The data are drawn from populations with a SD of 1.9 GMFM units. Consequently, 16 participants are needed per group (N=32). Considering 25% potential dropouts, 40 participants will be included.

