### RCT2: Low- to Moderate-Dosage Home Follow-Up Interventions (9-Week HABIT-ILE@home Follow-Up vs Nonspecific Home Follow-Up)

#### Overview

For the RCT2, all children will take part in a low- to moderate-dosage home follow-up intervention, either with a specific HABIT-ILE@home follow-up or with a nonspecific home follow-up program managed by the children’s usual therapists. In both groups, the follow-up program will last 9 weeks, with a recommendation of 5 hours per week of therapy at home. The 45-hour follow-up dosage (5 h/wk for 9 wk) was selected to provide a feasible home-based intervention for families while remaining comparable to previous HABIT-ILE protocols and above dosage ranges previously associated with clinically meaningful motor improvements in children with CP [13,25]. The amount of therapy time actually spent by the children and the type of exercises actually performed will be documented using the same form in both groups, which families will be asked to complete weekly throughout the 9-week follow-up period. In cases where therapists do not wish to provide a specific home program, families will be offered a home exercise booklet developed by the Fondation Paralysie Cérébrale during the COVID-19 pandemic.

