#### Nonspecific Home Follow-Up (Control Group)

For the 22 children who will receive the nonspecific follow-up at home in addition to their usual care, we will contact their usual therapists (OT or physiotherapist) and ask them to create a 5-hour weekly home program based on their usual practice for 9 weeks. This follow-up will correspond to heterogeneous therapist-driven interventions reflecting usual clinical practice, with no standardization of content imposed by the research team. This approach was chosen to reflect real-world clinical settings and the heterogeneity of rehabilitation practices between therapists, while ensuring a comparable amount of therapy time between the HABIT-ILE@home follow-up and nonspecific home follow-up groups.

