#### RCT2: Low- to Moderate-Dosage Home Follow-Up Interventions (9-Weeks HABIT-ILE@home Follow-Up vs Nonspecific Home Follow-Up)

Changes within each group during follow-up (T2-T1) will be assessed using paired-sample *t* tests when data are normally distributed, or Wilcoxon signed-rank tests in the case of nonnormal distributions.

The superiority analysis will be based on between-group comparisons using an analysis of covariance (ANCOVA) model. For each outcome, the model will be specified as outcome at T2 ~ outcome at T1 + RCT1_group × RCT2_group. This model will include the baseline value at T1 as a covariate and will test the main effects of the initial intervention (HABIT-ILE@home vs on-site), the follow-up intervention (HABIT-ILE@home follow-up vs nonspecific home follow-up), and their interaction. This approach will allow the effect of the second randomization (RCT2) to be evaluated while accounting for the initial allocation in RCT1.

The inference for superiority will be based on the main effect of RCT2_group (HABIT-ILE@home follow-up vs nonspecific home follow-up), adjusted for T1 values and RCT1_group. The interaction term (RCT1_group × RCT2_group) will be examined to explore whether the effect of the follow-up intervention differs depending on the initial intervention.

For normally distributed outcomes, model assumptions will be checked and standard ANCOVA estimates will be used. If normality is not verified, a nonparametric alternative based on rank-transformed ANCOVA will be applied.

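### The RCT2 power claim credits the whole pro-rata HABIT-ILE gain to the between-group difference, so the 80% for exceeding the 2-unit margin holds only if the active control arm shows about zero net change

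*Protocol article*

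**What the plan says.** The RCT2 paragraph under Sample Size in the protocol article takes its effect from an earlier HABIT-ILE study: "In that study of school-aged children, the duration of the intervention was 84.5 hours and the GMFM-66 increased by 7 GMFM units". It continues: "We thus hypothesized that, for 45 hours of intervention, there would be a true difference of 3.75 GMFM units between groups". It then sets a margin: "We estimate that the superiority margin will be 2 GMFM units since this value is the MCID of the GMFM-66". The other inputs are a 2-sided superiority t test, alpha 0.05, power 0.8 and SD 1.9. The result is 16 per group, raised to 40 in total for dropout. Study Design in fact splits each RCT1 group of 22 into 11 and 11, which gives 22 per RCT2 arm.

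The control arm is active. Study Design says: "Recommendations of practice schedule given to caregivers will be similar for both follow-up groups: 5 hours per week at home for 9 weeks". The RCT2 intervention overview repeats it: "In both groups, the follow-up program will last 9 weeks, with a recommendation of 5 hours per week of therapy at home". The control-group section has the research team ask each child's usual therapist for a 5-hour weekly programme, "while ensuring a comparable amount of therapy time between the HABIT-ILE@home follow-up and nonspecific home follow-up groups".

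The RCT2 part of Statistical Analysis specifies an ANCOVA of the T2 value on the T1 value and both group factors. It states: "The inference for superiority will be based on the main effect of RCT2_group". It names no margin.

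**The concern.** The 7-unit figure is a change within treated children. Scaled to 45 h, it estimates what the HABIT-ILE@home follow-up arm might gain. It equals the difference between arms only if the control arm's net change is zero. Both arms are recommended 45 h, and only content and supervision differ by design, so a gain proportional to hours that is credited to one arm alone does not fit the comparator described. The sample-size paragraph neither states nor defends the zero.

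At stake is how an RCT2 result would be read against the 2-unit margin. If both programmes help, the difference can fall short of 2 units, or fail to exceed it convincingly, while the HABIT-ILE@home follow-up is still the better of the two. A reader who trusts the stated 80% could take that outcome as evidence that the follow-up adds nothing.

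**Working it through.** **Inputs.** From the RCT2 sample-size paragraph: 7 units, 84.5 h, 45 h, difference 3.75, margin 2, SD 1.9, alpha 0.05, 16 per group. From Study Design: 22 per arm. Assumed here, because the article gives no figure: a net control gain c from T1 to T2 of 0 to 2 units (2 being the article's MCID), with the treated arm gaining the full 3.75.

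**The effect.** 7 × 45 / 84.5 = 3.73, stated as 3.75. Nothing is subtracted for controls.

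**Formula.** Two-sample noncentral t with n per group, df = 2n − 2 and noncentrality (3.75 − c − M) / (1.9 × √(2/n)), where M is the null value (2 or 0). Power is the probability of exceeding the critical t at 0.05 (one-sided) or 0.025 in the upper tail (two-sided).

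**Reproducing 16 per group.**
- Difference 3.75, margin 2, one-sided 0.05: 3.75 − 2 = 1.75. With n = 16, the noncentrality is 1.75 / (1.9 × √(2/16)) = 2.61 and power is 81.6%. The smallest n for 80% is 16, which matches.
- The same at the stated two-sided alpha: 20 per group are needed. With 16, power is 71.3%.
- Difference 3.75 against 0, two-sided: 6 per group.
- Difference of exactly 2 against 0, two-sided: also 16 (79.5% with 15, 82.1% with 16). On this reading 3.75 plays no part.

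So 3.75 leads to 16 only through the margin at one-sided 0.05, but the article does not show which calculation was run.

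**Power over assumed control gains** (each cell: 16 per group / 22 per group):

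| Control gain c | Difference | Margin 2, one-sided 0.05 | Margin 2, two-sided 0.05 | Null 0, two-sided 0.05 |
|---|---|---|---|---|
| 0 | 3.75 | 81.6% / 91.3% | 71.3% / 84.7% | >99% / >99% |
| 0.5 | 3.25 | 56.9% / 69.2% | 43.7% / 56.8% | 99.7% / >99% |
| 1.0 | 2.75 | 29.0% / 36.1% | 19.0% / 24.8% | 97.7% / 99.7% |
| 1.5 | 2.25 | 10.0% / 11.2% | 5.5% / 6.3% | 90.0% / 97.0% |
| 2.0 | 1.75 | 2.2% / 1.9% | 1.0% / 0.9% | 71.3% / 84.7% |

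**Largest control gain that still leaves 80% power** (16 / 22 per group): 0.04 / 0.30 for the margin at one-sided 0.05; about −0.2 / 0.11 for the margin at two-sided 0.05; 1.81 / 2.11 against 0. At two-sided 0.05 with 16 per group, the margin claim therefore needs controls to decline slightly.

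Against the margin, the sample size for 80% power at one-sided 0.05 rises from 16 per group at c = 0 to 30 at c = 0.5 and 81 at c = 1.0. From c = 1.75 no sample size suffices, because the true difference is then 2 or less.

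These figures use the article's own t-test framework. Any precision gained from the ANCOVA covariate is not counted.

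**The case against.** Three arguments on the other side have weight.

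1. **The planned test has no margin.** For RCT1 the analysis section explicitly compares the confidence interval with a margin; for RCT2 it does not, and the stated hypothesis is only that the treated arm does better. Against 0, power with 22 per arm is at least 84.7% for control gains up to 2 units. This stands, and it confines the point. A reader might infer that RCT2 is underpowered as a whole; the document does not support that. Only with 16 per group and a control gain above 1.81 does the test against 0 drop below 80%.

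2. **Zero net control change may be reasonable.** The endpoint starts right after an intensive camp, and the Background warns of skill loss: "Maintaining the skills acquired during the 2-week intervention requires daily practice". A control programme might do no more than hold the gains, its content is not standardised, and 5 h per week is a recommendation rather than a delivered dose. This also stands in part. A reader might infer that controls will improve and that 3.75 is wrong; no control gain is documented, so that goes too far. But the Background ties loss to lack of practice, controls are given practice, and post-camp loss could equally reduce the treated arm's net gain. The sample-size paragraph makes none of these arguments.

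3. **The 16 may not come from 3.75.** A two-sided test of a 2-unit difference also gives 16, in line with the stated sidedness, and would already cover a control gain of 1.75 (3.75 − 2). So it cannot be asserted that the enrolled number depends on the zero assumption. However, the paragraph presents 3.75 as the true difference and 2 as the margin, and the power claim read that way is the one that fails.

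An article may leave the rationale for an effect size to the full protocol. The difficulty here is not brevity: the derivation that is printed does not match the comparator that is described.

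**Conclusion.** The point holds in a limited form. The RCT2 sample-size paragraph uses the entire pro-rata HABIT-ILE gain as the between-group difference and so implicitly sets net control change to zero in an arm recommended the same 45 h. The stated 80% power for exceeding 2 units then requires both about zero net control change and a one-sided alpha that the paragraph does not state. With 16 per group, half a unit of control gain lowers power from 82% to 57% at one-sided 0.05; at the stated two-sided alpha it starts at 71% and falls to 44%.

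The size of the loss rests on assumed control gains, on SD 1.9, and on the treated arm gaining 3.75. The main-effect test against 0 is not endangered within the assumed range at planned enrolment. Severity is minor to moderate: a stated figure and its interpretation need correcting, not the design.

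**What to change.** Enrolment and sample size stay as they are.

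- In the RCT2 sample-size paragraph, say that 3.75 assumes no net control change from T1 to T2, and give the reason if there is one.
- Restate power at the stated two-sided alpha over assumed control gains of 0 to 2 units, both for the planned test against 0 and for the 2-unit margin. Fix that range without using the observed data, since the article reports data collection and analysis as complete.
- State that RCT2 superiority rests on the ANCOVA main effect tested against 0, as the analysis section already implies, and that the 2-unit value is a benchmark for clinical relevance.
- Report the adjusted effect with its 95% CI against both 0 and 2 units, and say that not exceeding 2 units is not evidence of no added value.

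The cost is a few sentences and a small table, with no new data. The downside is that the stated power for the 2-unit claim becomes visibly weaker.

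### RCT2's 16 per group does not follow from its stated inputs: a 2-sided .05 test against a 2-unit margin needs 20 completers per group, and 16 give about 71% power

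*Protocol article*

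**What the plan says.** All the inputs are in the RCT2 part of the Sample Size section of the protocol article.

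- Test: "for a 2-sided superiority *t* test comparing 2 independent means".
- Assumed effect: "there would be a true difference of 3.75 GMFM units between groups". It is scaled from a 7-unit gain over 84.5 hours to 45 hours of follow-up.
- Error rates: "with an α of .05 and a 1-*β* of 0.8".
- Margin: "We estimate that the superiority margin will be 2 GMFM units since this value is the MCID of the GMFM-66".
- Spread: "The data are drawn from populations with a SD of 1.9 GMFM units".
- Result: "Consequently, 16 participants are needed per group (N=32). Considering 25% potential dropouts, 40 participants will be included".

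The Study Design section fixes the number actually allocated: 44 children enter RCT1, and "each group will then be further randomized into 2 subgroups of 11 participants (RCT2". That makes 22 per follow-up arm. The RCT2 part of the Statistical Analysis section rests the superiority claim on the main effect of follow-up group in an ANCOVA adjusted for the T1 value and the RCT1 group. It does not mention a margin.

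**The concern.** The section gives every quantity needed to recompute the sample size, and the result does not match. A 2-sided test at .05 places .025 in the tail that matters for superiority. Sixteen per group looks small for a distance of 1.75 units between margin and assumed effect with an SD of 1.9.

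The change in GMFM-66 from T1 to T2 is the primary outcome of RCT2. Readers will judge a null or borderline result against the claimed 80% power, and they will take the superiority claim to be held at the error rate the text names. If the calculation used a different sidedness or a different null value, neither reading is safe. The dropout step adds a second mismatch: 40 does not deliver the section's own 32 completers, and it is not the number randomized.

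**Working it through.** **Inputs** (RCT2 sample size section): true difference 3.75, margin 2, SD 1.9, alpha .05 2-sided, power 0.80. Equal allocation comes from the Study Design section.

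**Method.** Two-sample t test of superiority by a margin, using the exact noncentral t distribution.

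- Distance from margin to assumed effect: 3.75 − 2 = 1.75.
- Standard error with n per group: 1.9 × √(2/n).
- Noncentrality: 1.75 / SE, with 2n − 2 degrees of freedom.
- Power: probability that the noncentral t exceeds the critical value (upper .025 for 2-sided .05, upper .05 for one-sided .05).

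**The stated figure, with the stated inputs (2-sided .05)**

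| n per group | SE | Noncentrality | Critical t | Power |
|---|---|---|---|---|
| 16 | 0.672 | 2.605 | 2.042 | 71.3% |
| 19 | 0.616 | 2.839 | 2.028 | 78.9% |
| 20 | 0.601 | 2.913 | 2.024 | 81.0% |

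The requirement is 20 per group (40 completers). The normal approximation gives 19. Using the unrounded difference, 7 × 45/84.5 − 2 = 1.728, still gives 20. Rounding or approximation therefore does not explain 16.

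**Routes that do or do not give 16**

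- Same inputs, one-sided .05: 15 per group gives 79.3% and 16 gives 81.6%, so 16 is the minimum. Only the sidedness has changed.
- 2-sided .05, a 2-unit difference tested against zero: 15 gives 79.5% and 16 gives 82.1%, so 16 is again the minimum. This route discards the 3.75 and uses 2 as the effect instead of as a margin.
- 2-sided .05, 3.75 tested against zero: 6 per group are enough.

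For comparison, the RCT1 calculation is labelled one-sided at .05. It reproduces its 17 per group (16 gives 89.7%, 17 gives 91.3%) if the true difference, whose value is not printed, is assumed to be 0.

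**Dropout**

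- 32 × 1.25 = 40, which is how the stated number arises.
- 40 × 0.75 = 30, or 15 per group, below the stated 32.
- 32 / 0.75 = 42.7, so 43. The 44 randomized cover this: 44 × 0.75 = 33.
- For the 2-sided requirement of 40 completers: 40 / 0.75 = 53.3, so 54. The 44 randomized do not cover this.

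**Power of the design as randomized, 2-sided .05 against the margin of 2**

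- 22 per arm, no loss: 84.7%.
- 16.5 per arm on average (33 children after 25% loss): 72.7%.

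**If there is no margin** (as in the RCT2 analysis section), with a true difference of 3.75 and SD 1.9: power exceeds 99% at 15, 16 or 22 per arm.

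**The case against.** Four points can be made for the plan.

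*The trial enrolled more than the stated number.* This stands in part. RCT1 set enrolment at 44, so the figure of 40 never governed the trial. With 22 per arm and no loss, power against the margin is about 85%. After the plan's own 25% loss it is about 73%, so the stated 80% holds only if losses are small: 20 of the 22 in each arm must complete.

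*The planned analysis has no margin.* This stands, and it limits what can be concluded. A reader might infer that RCT2 really has about 71% power. The documents do not support that as a property of the trial. The 71% belongs to the margin test described in the sample size section; against zero, a true 3.75 would be detected almost certainly. The point does not rescue the calculation, because dropping the margin gives 6 per group, not 16.

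*The ANCOVA may reduce the residual SD.* That is possible. As an assumption, if the covariate shrank the stated SD by √(1 − r²), r of about 0.45 would bring the 2-sided requirement down to 16. The document gives no correlation and states that the calculation was for a t test, so this cannot be its basis.

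*The cause is not known.* This also stands. A reader might conclude that 16 is a one-sided figure mislabelled as 2-sided. That is the most economical explanation, since it changes one input, but the PASS output is not shown and a second route gives the same number. Under either route the section misdescribes what was computed.

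**Conclusion.** The concern holds in this form: 16 per group does not follow from the inputs printed beside it. Under those inputs (2-sided .05, difference 3.75, margin 2, SD 1.9, t test, equal arms) 20 completers per group are needed, and 16 give 71.3% power instead of 80%. The one-sided origin is probable but unconfirmed. The dropout figure of 40 falls two short of its own target of 32, with little practical effect because 44 were randomized.

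The power of RCT2 cannot be stated until the test is settled. It is about 73% to 85% against the 2-unit margin at 2-sided .05, depending on losses from 25% to none, and above 99% against zero if the true difference is 3.75. All of these figures take the SD of 1.9 as given.

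**What to change.** 1. Report the sidedness, null value and margin used in the original PASS run, and correct the RCT2 sample size text to match. Since data collection is complete, this should be read from the stored run and not chosen now.
2. If the test is 2-sided .05 against a margin of 2, state that 20 completers per group are needed for 80% power, and that the 44 randomized give about 73% after 25% loss and about 85% with none.
3. If the run was one-sided at .05, say so and remove the 2-sided label. If it was a 2-unit difference against zero, say that, and do not describe 2 as a margin or 3.75 as the difference the calculation used.
4. Give the enrolled number as 44 in this section. Do not present it as the dropout-inflated requirement for the 2-sided margin test, which would be 54.
5. Reconcile this section with the RCT2 statistical analysis section: either the superiority claim is judged against the 2-unit margin, or the power statement is rewritten for a test of the main effect against zero. The stated power must belong to the test that is performed.

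The cost is a text correction. No participants are added, and no data collection changes.
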